**Fig. 1 Fig1:**
[figure not shown]
Study flowchart

#### Interventions

##### Control group

Parents allocated to the active control arm will receive a structured power-point presentation on parenting and child development issues, called “Raising Healthy Children” (duration: 1 to 1.5 hours). The structure and contents were developed by University of Bremen and reviewed by the project partners, and the material is available upon request. Four topics will be covered: (1) Stages of child development; (2) Potential risk factors for child internalising problems; (3) Resources and protective factors; (4) Tips: What parents can do to promote children’s development. The choice of this comparator was made so as to ensure that parents from the active control benefit from useful information in dealing with their children (given that all recruited participants reported having a child with elevated levels of behavioural difficulties will have children with behavioural problems). At the same time, when conceiving the lecture, we made sure we minimised the effects of potential confounds in the control group that would make it similar to the intervention, such as details on parenting strategies, programme length, non-didactic approach (lecture in this group versus collaborative work in the intervention group), and hands-on activities (no home activities for this group).

Facilitators delivering this lecture will have the same/similar expertise to that of the facilitators engaged in PLH. Facilitators will participate in a brief training explaining the purpose of the lecture, clarifying the contents and addressing potential concerns. They will also be trained to follow the protocol to minimise risk of contamination between the two conditions (e.g. only allow minimal discussion within the lecture, answer questions in a didactic way).

##### Intervention group

The optimised version of PLH-YC will be delivered over five weekly sessions using a participatory, non-didactic approach to engage parents in learning positive parenting and child behaviour management skills. Programme activities include illustrated comics modelling how to implement key parenting skills, home activity assignments to apply these skills with their children, and group discussions addressing challenges experienced when applying home activities. The programme also includes simple mindfulness stress reduction exercises such as “Taking a Pause” to help parents cope with stress and reactivity towards their children. There is a facilitator manual for each session, and parents receive a PLH parent book (long versions in English, Macedonian, and Romanian available here: https://rise-plh.eu/work-packages/work-package-2/). For the current study, the facilitator manuals and parent handbooks of the optimised intervention will also be translated into Albanian and Russian. If the programme is delivered in person according to the standard protocol, each PLH-YC group with 12 parents will be delivered by two facilitators. Locally recruited professionals and non-professionals (e.g. teachers, psychologists, social workers, and peer parents) with prior experience delivering the programme during Phase 2 of the RISE project will serve as facilitators. All facilitators participated in a 40-h standardised training prior to delivering the programme for the first time. They will also receive an additional 16-h booster training prior to the RCT.

Programme and lecture delivery will start as soon as the programme implementers can organise a group of approximately 12 participants per condition who have completed baseline assessments. Facilitators of both groups will receive supervision on demand by trained coaches who have also previously provided coaching to facilitators during Phase 2.

##### Intervention contingency plan in the context of SARS-CoV2 pandemic

All three countries face significant challenges in dealing with the COVID-19 pandemic, challenges that might seriously interfere with the trial implementation. The stepwise safety plan is based on local restrictions and the CORONA traffic light system (https://vis.csh.ac.at/corona-traffic-light/world/) and includes (a) applying safety measures to reduce risk of infection during in-person meetings (e.g. keep distance, wear masks); (b) reduce the PLH parenting group size to six parents and one facilitator per in-person group (instead of 12 parents and two facilitators per group); and/or (c) switching to online video-conference delivery in areas where in-person delivery is no longer possible (PLH-YC: six parents per group + one facilitator, lecture: 12 parents per group + one facilitator). In these situations, we will deliver the optimised PLH programme and the lecture online via video-conferencing technology (e.g. Zoom, Microsoft Teams, or another secure platform in compliance with the GDPR and ethical guidelines for data safety). Facilitators of both conditions will receive a brief training on how to conduct the groups via online meeting software.

### Compensation of participants

Caregivers will receive a voucher (8–20€) and a snack (in-person assessment only) per assessment. The value varies between countries, because the buying power of a preset amount of money is different across countries. Also, if parents participate in all three phone calls (daily ratings between pre- and post-assessment), they will receive a gift. Any second caregiver participating in assessments will also receive compensation. This will be smaller given that the assessment is much shorter.

Parents from both groups will receive a snack (or a food voucher for the same amount), childcare, transportation support (if needed) for each session when delivered in-person, and a certificate of completion at the end. In the PLH-YC intervention group, parents participating in at least four out of five sessions will get a small gift. If interventions are carried out online because of the restrictions imposed by the COVID-19 pandemic, participants will receive internet cards or another voucher of the same amount to ensure that barriers for participation (i.e. connectivity issues) will be removed.

### Study outcomes

#### Primary outcome

*Child aggressive behaviour* will be assessed with the respective subscale of the parent-report Child Behavior Checklist (CBCL) 1½–5 and 6–18 years old [43]. Parents rate the occurrence of certain behaviours of their child on a 3-point Likert Scale (0 = *not true* to 2 = *very true* or *often true*).

*Child externalising disorders* will be evaluated by using The Mini International Neuropsychiatric Interview for Children and Adolescents – Parent Version (MINI-KID-P) [44]. The MINI-KID-P will be used to assess whether the criteria (based on ICD-10 and DSM-5) for (a) Conduct Disorder (CD) (F91.1, F91.2, F91.9) or (b) Oppositional Defiant Disorder (ODD) (F91.3) are met (yes/no). The results of the two disorders will be combined to one binary total score with 0 = *no externalising disorder* and 1 = *current externalising disorder* (ODD or CD).

On three occasions between baseline and post-test assessments, Parent Daily Ratings (PDR) [45] will be used to monitor *child oppositional and aggressive behaviour problems* that occurred within the last 24 h (answer format: *did occur/did not occur*). In order to minimise drop-outs, we will only administer the oppositional and aggressive subscale (10 items + 2 positive items) instead of the full PDR. We excluded the last item from the subscale (“he/she pouts”) because this question caused translation problems in the three implementation countries. The item was not understood correctly by parents and assessors and thus did not result in valid answers. The PDR will be assessed over the phone three times between pre- and post-assessment.

#### Secondary outcomes

*Child internalising problems* will be evaluated by using the internalising subscale of the parent-report versions of the CBCL 1½–5 and 6–18 years old [43]. The internalising subscale raw scores range from 0 to 62 (CBCL 1½–5 version; 31 items) and 0 to 64 (CBCL 6–18 version; 32 items) with higher scores indicating more problems.

*Parenting behaviours* will be assessed in four ways. The Laxness and Over-reactivity Subscales of the Parenting Scale will be used, measuring dysfunctional parenting practices [46]. Second, we apply self-reported measures of positive parenting and effective discipline (Parenting of Young Children Scale) [47]. Third, we will add five items from the Alabama Parenting Questionnaire (APQ) phone interview (three items for positive and two for negative parental behaviours) [48, 49] to the PDR phone assessment for assessing daily reports of effective parenting behaviour. The APQ answer format was adapted to fit the PDR format (*did occur/did not occur*). Fourth, child maltreatment will be assessed using the ISPCAN-Child Abuse Screening Tool – Trial-Children (ICAST-TC) [50].

For *parent-child relationship*, the Five-Minute Speech Sample (FMSS) [51, 52] will offer insight into caregivers’ attitudes and feelings about their child and the quality of the relationship. The parent is instructed to talk about his/her child for 5 min. The parent’s response will be audio recorded. The parent-report is then rated by trained coders, e.g. with regard to coherence, as an indicator for parent-child relationship [53]. We will also use the subscales Warmth and Criticism of the Family Affective Attitude Rating Scale (FAARS, [54]).

*Parental mental health* measures will tap into depression, anxiety, and stress symptoms by using the eponymous DASS-21 [55]. Three subscales can be derived, measuring caregiver symptoms of stress, anxiety, and depression (seven items each subscale). Total DASS scores range from 0 to 63, with subscales from 0 to 21.

*Parenting stress* will be measured using the Parenting Stress Scale (18 items, [56]). *Parental relationship measures* will include assessments of intimate partner violence and relationship quality. Intimate partner violence (physical and psychological victimisation and perpetration) will be evaluated with a screening instrument—family maltreatment measure [57] and adapted short form of the Revised Conflict Tactics Scale (CTS2S) comprising 29 items [58]. Couple satisfaction will be assessed using the Couple Satisfaction Index (4 items) [59].

*Child quality of life* will be measured using the Child Health Utility 9D (CHU9D; nine items). The sum score of the CHU9D ranges from 9 to 45, with higher scores indicating lower levels of quality of life.

#### Implementation outcomes

*RE-AIM Reach measurements* will comprise enrolment rate (total number of caregivers who attend the first session of the PLH/ the lecture group divided by the number of families recruited in that condition) and, for the PLH groups, the participation rate (percentage of the five sessions attended).

With regard to *RE-AIM implementation quality*, for both groups, programme implementation will be assessed in terms of implementation fidelity and adherence. The number of total activities actually implemented (yes/no), divided by the number of activities by facilitator (assessed via a facilitator checklist) required in the PLH-YC programme manual/lecture content, will be used as an indicator of *implementation fidelity.* Fidelity assessments will be self-reported by facilitators as well as assessed by external raters during live coded sessions (see below).

For *quality of delivery*, *competent adherence* of PLH facilitators to the programme activities and their delivery skills will be assessed with the PLH-Facilitator Assessment Tool (PLH-FAT) [32]. Trained assessors will attend one to two sessions to do live codings using the PLH-FAT. Seven distinct behavioural categories will be grouped into two scales, describing core activities and process skills. The assessment of core activities comprises modelling skills, collaborative work between facilitators, engaging participants, and leadership skills. Coaches assessing facilitators will not be blind to allocation. The delivery skills of the lecture facilitators will be assessed with one overall quality of delivery item (0 = inadequate, 4 = excellent), which will be rated by trained coders.

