If the optimised programme is effective, a secondary objective of the RISE project is to explore the implementation and scalability of PLH-YC to enable wide-spread and sustained use of the optimised parenting programme in the Southeastern European countries. We will apply the steps of the RE-AIM model [38] to translate the learning from implementation of the evidence-based programme into sustainable practice. Moreover, we will report on the cost-effectiveness of the programme and other service use by parents in the PLH-YC and control conditions during, and after the intervention across the three countries.

The secondary aims and hypotheses are:
Examine the cost-effectiveness of PLH-YC in comparison to a lecture on parenting on the *primary outcome* of child aggressive behaviour and the economic impact of the programme, including potential costs for future dissemination and scale-up. Impact on other outcomes such as dysfunctional parenting, positive parenting, and child quality of life will also be used to better inform decision-making.To assess the role of socio-economic, contextual and individual factors (i.e. family adversity, parental mental health, intimate partner violence, couple dissatisfaction, and child aggressive behaviour at baseline) on the implementation of PLH-YC in the three countries. We will examine implementation in hypotheses a–c in two ways. We will examine these associations with enrolment (attended 1st session) across groups. We will also examine the associations with participation rate in the PLH-YC condition (percentage of sessions attended). The hypotheses are:

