## Methods

### Study design

We aim to recruit 864 primary caregivers of children aged 2 to 9 years old from North Macedonia, Romania (both classified as upper middle-income countries; the World Bank categorised Romania as high-income country based on 2019 per capita income for the first time) and Republic of Moldova (lower middle-income country; *n* = 288 per country). Participants will be randomly allocated to one of the two parallel study arms: control group (consisting of a lecture) or a parenting intervention group receiving a five-session PLH-YC programme.

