#### Recruitment

Recruitment of participants and baseline assessments are scheduled to take place from December 2020 to February 2021 in all three countries, a timeline which loosely corresponds to the middle of the 2020/2021 school year. However, the COVID-19 pandemic might cause some variation as study teams follow national policies and timelines regarding the new school year and access to schools.

Potential participants will be referred to the study by school counsellors, teachers and educators, or community workers. Additionally, all countries will advertise and provide study information on relevant websites and social media pages. On first contact with the research team, parents will be assessed for eligibility, and scheduled for providing informed consent and pre-assessment data. After the baseline assessment, they will be randomly allocated to one of the study conditions. During the recruitment stage, we will encourage secondary caregivers (i.e. fathers, grandparents, social tutors) to enrol for assessment and to take part in the programme, alongside primary caregivers.

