#### Group allocation and allocation concealment

Prior to randomisation, all countries will identify and select a sample of recruitment sites (schools, kindergartens, community, and social services centres) covering different neighbourhoods, geographical areas, ethnic compositions, and socio-economic strata in and around Skopje (North Macedonia), Cluj-Napoca (Romania), and Chișinău (Republic of Moldova).

Randomisation will be coordinated by one of the project partners (University of Klagenfurt) using an online randomiser, https://www.randomizer.org/ (*N* = 288 per country, 864 in total). Participant numbers will be randomised to the PLH-YC programme or the control condition after completion of the baseline assessment based on the randomisation list (individual 1:1 randomisation in blocks of 24). The randomisation list will be provided to the team in Bremen, who will be contacted after each participant is enrolled to unveil their assignment. This threefold procedure allows the analysis team to remain blind to group assignment, ensures that assignment occurs independently and ensures that teams in each country receive allocation information after enrolment.

Participants will be allocated to groups after completion of the pre-assessment. Thus, outcome assessors and participants will be blinded to group allocation at pre-assessment. All data assessors conducting pre-test, periodic, post-test, and follow-up interviews with parents will be blinded regarding the allocation of participants to the groups to minimise evaluation bias: The implementation of the intervention will be conducted by different staff (programme coordinators and facilitators) than the assessments. Thus, data assessors will be unaware of the group allocation of participants at the later assessment points (periodic, post, follow-up). To ensure that participants do not reveal their group allocation during the post- and follow-up assessment to the assessor, the data assessor will ask the participants to not share the group allocation at the beginning of the interview. Only in cases where the parent reports a (serious) adverse event, will the group allocation be unblinded (during periodic  and follow-up assessments). Upon completion of the pre-test measurements, caregivers will be notified of their allocation status.

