#### Data analysis

##### Sample size calculation

To allow detection of small effect sizes, we will estimate sample size based on a *d* = .25 (*f* = .10) for the primary outcomes. Detecting this effect in a repeated measures ANOVA at an alpha of .05 whilst ensuring a power of 80% requires a total sample of *N* = 704. We will examine the change in the primary outcomes across three time points (pre, post, and follow-up) within the overall sample using latent growth modelling and conduct a multi-group analysis to test differences across countries. To reach the required sample size of 704, we will recruit a total of 864 families for baseline assessment, assuming approximately 17% drop-out rate based on our previous phase of data collection [69].

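### The enrolment rate counts caregivers in the numerator and families in the denominator, so applied as worded it overstates Reach and can exceed 100%

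*Protocol article*

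**What the plan says.** The protocol article, under Implementation outcomes, gives two RE-AIM Reach measures. The one that applies to both arms is the enrolment rate, defined as the "total number of caregivers who attend the first session of the PLH/ the lecture group divided by the number of families recruited in that condition". The other applies to PLH-YC only: the percentage of its five sessions that were attended.

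The Recruitment section says of other family members: "we will encourage secondary caregivers (i.e. fathers, grandparents, social tutors) to enrol for assessment and to take part in the programme, alongside primary caregivers". The enrolment definition does not restrict the numerator to primary caregivers or to one person per family.

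The recruited unit is worded in two ways. Study design has "We aim to recruit 864 primary caregivers of children aged 2 to 9 years old", and Sample size calculation has "we will recruit a total of 864 families for baseline assessment". The total is the same, so there is one primary caregiver per family and the denominator counts each family once.

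Enrolment reappears in the secondary aims, under Overview and aims of the present study: "We will examine these associations with enrolment (attended 1st session) across groups". The section on primary and secondary outcome analyses names the enrolment rate as the mediator across both arms.

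**The concern.** A rate of this kind is a proportion only if every unit in the numerator is also a unit in the denominator. Here the two coincide only when exactly one caregiver can be counted per family. The article plans for more than one: second caregivers are invited into the programme, have their own short assessment and compensation, and are the subject of a possible parent-gender moderation analysis.

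The rate is the only Reach measure defined for both arms, and Reach feeds the article's objective on implementation and scalability. An analyst following the sentence literally would report a figure that mixes two things: how many families turned up, and how many people each family brought. A reader would take it as the first. The definition also leaves open whether a family counts when only the second caregiver comes.

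**Working it through.** The article reports no enrolment rate, so there is no figure of its own to reproduce. The check is of the formula.

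**Inputs from the article**
- Families in total: 864 (Sample size calculation).
- Allocation: "individual 1:1 randomisation in blocks of 24", so 864 / 2 = 432 families per condition.
- Numerator: caregivers at the first session. Denominator: families (Implementation outcomes).

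**Inputs assumed, because the article gives neither**
- f, the share of families with someone at the first session: 0.70, 0.80 or 0.90.
- s, the share of those families bringing one second caregiver: 0.10, 0.20 or 0.30.

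**Formulas**
- Family-level rate = (432 × f) / 432 = f, which cannot exceed 1.
- Rate as worded = (432 × f + 432 × f × s) / 432 = f × (1 + s).
- The ratio of the two is 1 + s, whatever f is.
- The rate as worded passes 100% when s > 1/f − 1.

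**Results**

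| f (family-level rate) | s = 0.10 | s = 0.20 | s = 0.30 | s above which the rate exceeds 100% |
|---|---|---|---|---|
| 0.70 | 0.77 | 0.84 | 0.91 | 1/0.70 − 1 = 0.43 |
| 0.80 | 0.88 | 0.96 | 1.04 | 1/0.80 − 1 = 0.25 |
| 0.90 | 0.99 | 1.08 | 1.17 | 1/0.90 − 1 = 0.11 |

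In whole families, f = 0.80 is about 346 of 432. With s = 0.30 the count of caregivers is about 450, and 450 / 432 = 104.2%.

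If the numerator is meant to hold primary caregivers only, s drops out and the rate equals the share of families whose primary caregiver attended. The whole discrepancy therefore depends on which caregivers are counted, and the definition does not say.

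**The case against.** The strongest reply is that double counting is one reading and not a stated rule. The article uses primary caregivers, families and participants for the same 864 units, and blocks of 12 per arm alongside groups of 12 parents suggest one counted parent per randomised unit. The authors are also unsure how many second caregivers will come. This stands as far as it goes: a reader should not infer that the plan deliberately counts couples twice, or that the inflation will be large. It does not remove the defect, because the sentence as written admits the double count and nothing else in the article rules it out.

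Two stronger readings are tempting, and the article does not support them.

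- *That the first-session rule is itself wrong, because a PLH-YC family attending only sessions 2 to 5 would be classed as not enrolled.* The secondary aims and Implementation outcomes state the same rule, so there is no contradiction. The article describes no late joining. Later attendance is kept in the participation rate, and actual participation enters the complier average causal effect models. Counting attendance at any session would give PLH-YC families five chances to qualify against one for lecture families, which would make the arms less comparable.
- *That the unit error biases the enrolment hypotheses and the mediator model.* A ratio per condition cannot serve as a participant-level variable, and attendance at the first session is naturally coded yes or no for each randomised participant. What remains is that the mediator is named as the enrolment rate, whose only full definition is the mismatched one, so the coding is worth stating.

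A reader might also infer that one arm or country would look better reached than another. That would need second-caregiver attendance to differ between them, and the article gives no figure on this.

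**Conclusion.** The point holds as a unit error in a secondary implementation outcome. Applied literally, the enrolment rate equals the family-level rate multiplied by (1 + s) and has no upper bound at 100%. The direction is certain under the literal reading whenever any second caregiver attends the first session. The size is not known: 77% to 91% in place of 70% rests on an assumed 70% family attendance, an assumed s of 10% to 30%, and at most one extra caregiver per family. Exceeding 100% needs higher values, for example s above 25% when 80% of families attend.

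No stated figure in the article changes. The sample size, the primary outcome and the primary comparison are unaffected. The first-session criterion is a consistent, deliberate definition and is not part of the error.

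**What to change.** Keep the first-session rule in both arms and correct the unit:

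1. Define the enrolment rate as the number of families with at least one caregiver at the first PLH-YC session or at the lecture, divided by the number of families randomised to that condition. If only the primary caregiver's attendance is meant to count, say so explicitly and use that in the numerator.
2. Use the same family-level yes/no indicator wherever enrolment appears in the secondary hypotheses and as the mediator across groups.
3. Report second-caregiver attendance as a separate descriptive rate in each arm.

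This is a change of wording. It assumes that attendance registers show who came from each family; if they record only head counts, they would need to identify the caregiver. The one downside is that the reported Reach may be slightly less favourable than under the present wording.

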### Participants and eligibility criteria

Potential parents or other primary caregivers will have the following inclusion criteria: (a) be aged 18 years or older, (b) be responsible for the care of a child between the ages of 2 and 9; (c) report at least subclinical levels of child’s behavioural problems as assessed with the oppositional defiant disorder subscale (ODD) of the Child and Adolescent Behavior Inventory (CABI, scores ≥ 10 will be included) [41, 42]; (d) have spent at least four nights a week with the child in the same household during the previous month and will continue to do; (e) agree to being randomised to one of the conditions; (f) consent to participate in the full study; (g) have adequate language skills to participate in the group /lecture, either in the primary language of the group or with additional language support provided. We will exclude primary caregivers whose children have been removed from their custody.

Inclusion criteria for facilitators are as follows: 1) aged 18 or older, 2) prior participation in a training workshop for the lecture/PLH-YC, 3) agreement to either deliver the lecture (one session) or PLH-YC (five sessions), 4) provision of consent to participate in the full study.

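### Both Reach measures count only families already randomised, so the enrolment rate is an upper bound on the share of otherwise eligible families reached

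*Protocol article*

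**What the plan says.** All references are to the protocol article.

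- **Implementation outcomes** gives Reach two components. The enrolment rate is the "total number of caregivers who attend the first session of the PLH/ the lecture group", "divided by the number of families recruited in that condition". The second is, "for the PLH groups, the participation rate (percentage of the five sessions attended".
- **Participants and eligibility criteria** makes acceptance of the trial itself part of inclusion: "e) agree to being randomised to one of the conditions; (f) consent to participate in the full study".
- **Recruitment** gives the order of steps before allocation: "parents will be assessed for eligibility, and scheduled for providing informed consent and pre-assessment data". Families arrive by referral from schools and community workers, or through advertising. The same section encourages secondary caregivers to join the programme.
- **Group allocation and allocation concealment** fixes when a family acquires a condition: "Participant numbers will be randomised to the PLH-YC programme or the control condition after completion of the baseline assessment".
- **Overview and aims of the present study** places RE-AIM under a secondary objective that applies if the programme proves effective, namely to "explore the implementation and scalability of PLH-YC to enable wide-spread and sustained use". It also hypothesises that greater family adversity at baseline goes with lower enrolment.

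No Reach measure in the article uses families referred, contacted or otherwise eligible as its denominator.

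**The concern.** The Background names failure to reach the most disadvantaged as a main risk when parenting programmes are rolled out. A reader who meets a high Reach figure in the results will take it as evidence on that risk. The plan's figure cannot supply such evidence. It starts counting once a family has come forward, met the criteria, consented, agreed to randomisation and sat through the baseline interview. If many otherwise eligible families stopped at one of those steps, the figure would be the same as if none had.

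The adversity hypothesis has the same limit. If adversity deters families from consenting or completing baseline as well as from attending the first session, some of the families it affects most have left before the association is estimated. A weak association among participants would then not show that disadvantaged families are reached as well as others.

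There is also a mismatch of units. The numerator counts caregivers and the denominator counts families. With secondary caregivers invited, the ratio can rise above the family-level rate, and could in principle exceed 1, unless one attendance is counted per family.

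**Working it through.** **Plan's own figure.** The article states no Reach value or target, so there is none to reproduce.

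**Inputs**
- Families to be randomised: 864 at 1:1, so 864 / 2 = 432 per condition (Study design; Group allocation and allocation concealment).
- First-session attendance among randomised families, e: not given. Assumed 70% to 90%, with 80% as the worked case.
- Randomised share of otherwise eligible families, r: not given. Assumed 0.25 to 0.90. Here *otherwise eligible* means meeting criteria (a) to (d) and (g), leaving aside (e) and (f), which are themselves agreement to the trial.

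**Identity**, with everything counted in families:

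attenders / eligible = (attenders / randomised) × (randomised / eligible) = e × r

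The plan reports e. Since r cannot exceed 1, e is never below e × r. The two are equal only if no otherwise eligible family is lost before allocation. The overstatement factor is e / (e × r) = 1 / r.

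**Worked case, e = 80%.** Attenders per condition: 0.80 × 432 ≈ 346. Losses before allocation precede any assignment, so each condition is given an equal share of the otherwise eligible families, 432 / r.

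| r (assumed) | Otherwise eligible families per condition | Share reached | Plan's formula | Factor 1/r |
|---|---|---|---|---|
| 1.00 | 432 | 346/432 = 80% | 80% | 1.00 |
| 0.90 | 480 | 346/480 = 72% | 80% | 1.11 |
| 0.75 | 576 | 346/576 = 60% | 80% | 1.33 |
| 0.50 | 864 | 346/864 = 40% | 80% | 2.00 |
| 0.25 | 1728 | 346/1728 = 20% | 80% | 4.00 |

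**Full assumed range.** The lowest share is 0.70 × 0.25 = 17.5% and the highest is 0.90 × 0.90 = 81%. The plan's formula would report 70% to 90%.

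The direction follows from the identity alone and needs no outside definition of Reach. The size comes entirely from the assumed r.

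**The case against.** The strongest case on the other side has five parts.

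1. **The measure is openly defined and suits its analytic uses.** It is called an enrolment rate and its formula is given. The aims and the section on primary and secondary outcome analyses use enrolment and participation as predictors and mediators and in complier models, all of which need randomised families. This stands. The ratio should be kept, and the problem is only that it is presented as Reach.

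2. **Not every refusal is lost.** A reader might infer that all refusals vanish. They do not: caregivers learn their allocation after baseline, and those who then stay away remain in the denominator and lower the rate. Only losses before allocation are invisible.

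3. **No inflated number is carried into a projection.** A reader might infer that the enrolment rate feeds the scale-up estimate. The article does not say so. The Cost-effectiveness analysis section bases the large-scale resource estimate on the cost-effectiveness results, and the link from RE-AIM to scalability is stated only in general terms.

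4. **The figure need not overstate uptake in routine delivery.** Some families will refuse randomisation or research interviews, which would not exist at roll-out. This stands. It means that e × r is no forecast of routine uptake either.

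5. **The adversity hypothesis cannot be tested more widely.** It concerns adversity measured at baseline, and families who leave earlier have no such data. This also stands. What remains is a limit on interpretation that should be stated; the analysis is not mis-specified.

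It is also fair to say that the study flowchart is not shown and that an article condenses a fuller protocol. Refusals may well be counted somewhere. That would make the remedy easier, but it would not change the definition of Reach that the article states.

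**Conclusion.** The point holds in a limited form. Both Reach measures are conditional on randomisation, so families who decline consent, randomisation or baseline are not counted. Counted in families, the enrolment rate is an upper bound on the share of otherwise eligible families reached, and the definition as written cannot support a conclusion about Reach. The size of the gap cannot be computed from the document; the factors of 1.11 to 4.0 above illustrate assumed values of r from 0.90 down to 0.25.

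The document does not support saying that scale-up estimates are biased by this figure, or that routine uptake is certainly overstated. It also does not show that the adversity association is attenuated, which is possible but not established.

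This is a minor point about a secondary implementation measure. It does not touch the primary outcome, the sample size or the treatment-effect estimates.

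**What to change.** 1. Keep the present ratio for the predictor, mediator and complier analyses. Label it *initial attendance among randomised families* and count numerator and denominator in families.
2. Add Reach by stage and by country, using the first-contact screening counts: (i) randomised / families meeting criteria (a) to (d) and (g); (ii) first-session attenders / randomised; (iii) the product of the two. Stage (i) precedes allocation, so it is common to both conditions.
3. Where reasons were recorded, separate refusals of the research from refusals of the programme.
4. State that the adversity-enrolment result applies only to consenting families with baseline data.
5. State that the product is not to be entered directly into scale-up or cost-at-scale estimates, because some refusals are of trial procedures absent at roll-out.

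**Cost.** Wording, plus a tabulation of screening counts. The Recruitment section says "On first contact with the research team, parents will be assessed for eligibility", so the counts should exist. Recruitment has closed (Trial status), so the change depends on their having been kept. The Reach figure will be lower and less favourable, partly because of research burden. Families recruited by advertising will have no outer denominator, since the number who saw the advertisement is unknown.
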